### Study conditions

#### Online self-help intervention

The self-help intervention is grounded in the theories of self-regulation and stress-coping, incorporating techniques of CBT and stress-management. The content of the program reflects four main components covered in eight lessons: activation, relaxation, changing maladaptive cognitions, and goal attainment. The program contains a combination of psycho-education, exercises, and assignments, all strengthened by motivation and support to increase the effectiveness and to minimize the attrition over time.

The intervention is offered through a secured website that contains the complete work program. Participants work on the intervention 1-2 hours a week for a period of 6-10 weeks. The program starts with an introduction, and participants are asked to think of a small activity to perform (e.g., taking a short walk; lesson 1). They are stimulated to perform this activity in the following weeks and to expand this to other activities. Furthermore, participants will be instructed to do relaxation exercises and to continue these exercises in the coming weeks (lesson 2). Thereafter, participants learn to identify and change irrational cognitions (by challenging negative thoughts) and to evoke a strong and positive feeling when they experience negative feelings (lessons 3-5). Furthermore, participants are guided to formulate a new, realistic, concrete goal (such as quit smoking) and work on the stepwise attainment of this goal (lessons 6-7). Finally, the participant will work on a concluding and summarizing lesson (lesson 8). All participants will receive support from a coach during the intervention (see below).

#### Waiting list control condition

Participants randomized to the control group will be placed on a waiting list and will receive the intervention after T2. They will receive an initial phone call to explain the procedures (to minimize attrition). Participants will receive minimal support from a coach (see below).

#### Support from a coach

Participants in the intervention group will be allocated to a coach, who will provide motivation and support throughout the program. During the first telephone contact, the coach will introduce the program, motivate the participant, and address technical aspects. Once a week, a prescheduled telephone call of approximately 15 minutes will be arranged between the participant and the allocated coach. Coaching will be provided through queries about the participant’s progress, motivational remarks, support in case problems are encountered, and encouragement to continue the program. Coaching will not include formal psychotherapy and will be provided until the participant completes the program or for a maximum of 10 weeks. If the participant is not finished with the program after 10 weeks, the coaching will end, but the participant can continue the program.

Participants in the control group will also be allocated to a coach, who will provide minimal support over 8 weeks. Participants will have a pre-scheduled weekly telephone call of approximately 5 minutes with the coach. The coach will address the well-being of the participant. Coaches will try to prevent participant dropout and monitor their depressive symptoms. When depressive symptoms or suicidal thoughts increase, the coach will act appropriately (see ethical precautions).

A protocol for coaching will be used, with guidelines available for the provision of support. Coaches will receive a short training to inform them about the study and the coaching procedures. After each telephone call, coaches will note the elements that were used during the call (e.g., motivation, support) to monitor treatment integrity. Coaches will be Master students in clinical psychology or individuals with a Master’s degree in the field of psychology. The coaches will have completed clinical courses during their Master’s degree program in which they learned communication skills, interview techniques, and treatment strategies. In addition, coaches will be selected in a personal interview on the basis of adequate communication skills for the support and motivation of participants. Coaches will be supervised by the researchers and a psychotherapist. Once every 2 weeks (every week during the first month of the study), the coaches and the main researcher will hold an intervision meeting. Coaches can discuss difficulties and questions with each other and the researcher. If a problem arises between intervision sessions, the coach may contact the researcher. The researcher and the coach can consult a psychotherapist if necessary.

### Ethical precautions

Coaches will monitor the well-being of participants in both the intervention and control groups. Each week, they will ask how the participant is doing. When depressive symptoms worsen or when suicidal thoughts increase, the coach will discuss this with the participant. The coach can refer the participant to the general practitioner or the HIV treatment center, if necessary. The coach can discuss this with the researcher and the psychotherapist. When a participant is referred for more intensive treatment from a psychologist or psychiatrist, the participant may continue with the study. As this may influence the outcomes, the referral will be added as a covariate in the analysis.

Participants will complete questionnaires to assess depressive symptoms during the course of the study. When depressive symptoms of a participant increase, the researcher will notify the coach about this. The coach will discuss this increase of symptoms with the participant and will act appropriately. These guidelines are also described in the protocol for coaches.

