### Participants

At least 200 participants who are PLH with mild to moderate depressive symptoms will be included. Participants will be approached in 23 of the 27 HIV treatment centers throughout the Netherlands during their regular visits to the HIV nursing consultants and doctors. To be eligible to participate in the study, a participant must meet all of the following criteria: being HIV positive, exhibiting mild to moderate depressive symptoms (defined as Patient Health Questionnaire 9 (PHQ-9) [22] score > 4 and < 20), age 18 and older, having sufficient knowledge of the Dutch or English language, able to access the Internet, having an e-mail address, and available for the next 8 weeks to work on the intervention.

An eligible participant who meets any of the following criteria will be excluded from participation in the study: being in the first half year following HIV diagnosis, having severe cognitive impairments (e.g., forgetfulness), exhibiting severe depressive symptoms (defined as PHQ-9 score of 20 or higher), experiencing suicidal ideation (indicated by a score > 1 on the suicide item of the PHQ-9), showing an absence of depressive symptoms (indicated by a PHQ-9 score of 4 or lower), undergoing treatment presently by a psychologist or psychiatrist, or on antidepressants for less than 3 months or has experienced a change of type or dose of antidepressants in the past 3 months. In case of severe depressive symptoms (using the set criterion) and/or suicide ideation, patients will be referred to their general practitioner or the HIV treatment center.

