#### Demographic variables and other information

A self-designed questionnaire will be used to ask participants about sex, age, educational level, nationality, marital status, sexual orientation, social support, disclosure of HIV positive status, alcohol and drug use, previous depressive and anxiety episodes, treatment of psychological symptoms, and physical health. This information will be used to describe the demographic and clinical characteristics of the sample. In the follow-up assessments, questions will be asked about the use of medication for psychological problems and treatment received from a psychologist or a psychiatrist since the start of the study. The use of medication and treatment received will be added as covariates in the analysis.

Furthermore, participants will complete a self-designed questionnaire about information regarding the HIV infection. Questions include time since the HIV diagnosis, how the infection occurred, symptoms of the infection, cluster of differentiation 4 (CD4) cell count, viral load, use of highly active antiretroviral therapy (HAART), medication adherence, and side effects of the medication. This information will be used to describe the HIV status and use of HAART by the sample.

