### Statistical analyses

A two-tailed alpha of .05 will be used for significance testing. All analyses will be based on an intention-to-treat (ITT) analysis, which includes all participants who were randomized to one of the groups at the beginning of the study [47]. Baseline differences between conditions will be investigated with chi-square tests for categorical variables and ANOVAs for continuous variables.

To examine the effect of condition on the depressive symptoms at the post-tests, longitudinal multilevel regression analysis (LMRA) will be conducted [48]. A two-level model will be studied: time at level 1 and participants at level 2. The variable time will have four categories indicating the four time points (T0–T4). The baseline (T0) will be used as reference category. The independent variable is condition, the dependent variable is the score on the PHQ-9 or the CES-D, and several covariates will be included in the model (e.g., sex and age). Multiple imputation for missing data is not necessary in LMRA because it can include participants with missing data on one or more time points [48]. The existence of an effect of HIV treatment center will be investigated exploratory.

Furthermore, Cohen’s d will be calculated to indicate within- and between-group effect sizes [49]. In addition, clinically important differences for individual change in depressive symptoms will be examined. Change scores of 5 or more from the pretest to the post-tests will be considered as clinical important differences for the PHQ-9 [50].

With regard to all secondary outcomes, we will study the pre-treatment versus post-treatment changes by using the analyses described above for the PHQ-9 and the CES-D. To examine moderators of the treatment outcome, LMRA will be conducted. Potential moderators will be entered individually. Interaction effects will be investigated (e.g., time x condition x moderator). A limited number of cross-product interactions will be examined, and we will correct for multiple testing. Furthermore, the QUINT (Qualitative Interaction Trees [51]) method will be used to identify subgroups for which the intervention is most effective, by exploratory investigation of the multiple moderators.

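### Referral, medication use and outside treatment arise after randomisation, yet the plan adds them as covariates to what appears to be its only effect model, so that model need not estimate the intention-to-treat effect

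*Protocol article*

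**What the plan says.** Under Ethical precautions, coaches follow participants' well-being in both arms: "When depressive symptoms worsen or when suicidal thoughts increase, the coach will discuss this with the participant". A participant who is referred to a psychologist or psychiatrist may stay in the study, and then: "As this may influence the outcomes, the referral will be added as a covariate in the analysis".

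Under Demographic variables and other information, the plan adds: "In the follow-up assessments, questions will be asked about the use of medication for psychological problems". The same items ask about treatment by a psychologist or psychiatrist since the study began. It concludes: "The use of medication and treatment received will be added as covariates in the analysis".

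Under Statistical analyses: "All analyses will be based on an intention-to-treat (ITT) analysis, which includes all participants who were randomized". One effect model follows, a longitudinal multilevel regression (LMRA) of PHQ-9 or CES-D on condition. Time is categorical with T0 as reference, and there is an open list of covariates for which sex and age are the examples. Imputation is judged unnecessary because LMRA can use participants with missing time points.

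**The concern.** An intention-to-treat effect compares the arms as randomised, whatever happens afterwards. Covariates fixed before randomisation can sharpen that comparison. Covariates that follow from treatment and from the evolving outcome can distort it.

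The three variables named are of the second kind. Referral is prompted by worsening symptoms. People "undergoing treatment presently by a psychologist or psychiatrist" are excluded at entry, so such treatment during the study is a new event. Stable antidepressant use is allowed at entry, so some medication use may predate randomisation, but the follow-up item does not measure a baseline covariate.

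The article gives four routes by which condition can affect these variables:
- the programme's intended effect on symptoms;
- different coach contact, "a prescheduled telephone call of approximately 15 minutes" each week in one arm against "a pre-scheduled weekly telephone call of approximately 5 minutes with the coach" in the other;
- coaches and researchers who know the allocation, with coaches making referrals;
- a T3 questionnaire sent only to the intervention arm, so an ever-treated variable would cover a longer period there.

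Two things are at stake. The estimated effect may be biased. Also, participants with no follow-up questionnaire may leave the model, because a mixed model tolerates a missing outcome but not a missing covariate.

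**Working it through.** **1. The plan's own figure.** Inputs (Sample size section): d = 0.50, two-sided alpha 0.05, power 0.80. The two-sample t-test needs 63.8, so 64 per group, as stated. Noncentrality is d√(n/2) = 0.50 × √32 = 2.83, giving power 0.80. With 15% dropout, 128 / 0.85 = 150.6, against the stated 150. The sample size is not in dispute.

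**2. Model for the check.** Random-intercept model for T0, T1 and T2 (controls have no T3):

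score = time + condition + condition × time [+ covariate] + person effect + error

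The effect is the condition × time contrast against T0.

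**3. Assumptions (not in the documents).**
- Scores have SD 1, and half the variance lies between persons.
- A person is referred (R = 1) when a noisy mid-study symptom state exceeds a threshold set to give 10-30% referral in controls.
- 70% of the effect is present by mid-study.
- The extra care lowers later scores by 0, 0.3 or 0.6 SD.
- 15% are lost at random after T0 (the protocol's rate).
- 400,000 simulated participants per scenario; simulation error is below 0.01.

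**4. Target.** With a the effect of extra care, the true ITT effect is d + a × (referral in intervention − referral in control). Example: 0.50 + 0.3 × (0.21 − 0.30) = 0.47.

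**5. Results (mean of T1 and T2, in SD).**

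| d | Referral, control / intervention | Extra care | True ITT | No covariate | Per person, main effect | Per person × time | Time-varying |
|---|---|---|---|---|---|---|---|
| 0.50 | 10% / 6% | 0 | 0.50 | 0.50 | 0.50 | 0.49 | 0.47 |
| 0.50 | 20% / 13% | 0 | 0.50 | 0.50 | 0.50 | 0.48 | 0.45 |
| 0.50 | 30% / 21% | 0 | 0.50 | 0.50 | 0.50 | 0.47 | 0.44 |
| 0.50 | 30% / 21% | 0.3 | 0.47 | 0.47 | 0.47 | 0.47 | 0.44 |
| 0.50 | 30% / 21% | 0.6 | 0.45 | 0.45 | 0.45 | 0.47 | 0.44 |
| 0 | 20% / 30% | 0 | 0 | 0.00 | 0.00 | 0.04 | 0.07 |
| 0 | 30% / 42% | 0 | 0 | 0.01 | 0.01 | 0.05 | 0.09 |

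The last two rows assume that more people are referred in the intervention arm at the same symptom level, as longer coach calls could bring about. Largest attenuation: (0.50 − 0.44) / 0.50 = 12%.

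**6. Power, for scale.** At 64 per arm and d = 0.45, noncentrality is 0.45 × √32 = 2.55 and power about 71%, against 80% at 0.50.

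**7. Participants kept at 15% dropout.**
- One value per person, taken from follow-up: 85% kept, with the T0 rows of the others lost too (150 × 0.85 ≈ 128; 200 × 0.85 = 170).
- Time-varying, set to 0 at T0: 100% kept.
- No post-randomisation covariate: 100% kept.

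**The case against.** The article says the analysis, not the primary analysis, and its example covariates are sex and age. That stands as a caution. But no other effect model is described and nothing confines these variables to a sensitivity analysis, so placing them in the primary model is a reasonable inference.

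A reader might infer that the analysis set becomes a completer set. The documents do not support that. Table 1 collects the questionnaire section holding these items at the same visits as PHQ-9 and CES-D. A time-varying covariate would therefore usually be missing only where the outcome is missing too. Participants are lost only under one value per person, and those lost have T0 alone, which says little about condition × time. Referral is made through coaches and may be known even for dropouts.

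A reader might also infer that bias and loss come together. In general they do not. A main effect per person leaves the contrast almost unchanged but can lose people. A time-varying covariate biases the contrast but loses essentially nobody extra. Only a per-person covariate crossed with time does both.

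A simple regression of one outcome on arm and baseline can show more attenuation, down to 0.40 SD and power of about 0.61. That is not the planned model, and the longitudinal check does not reach those figures. Nor is 64 per arm the recruitment aim: with 200 randomised and 15% lost, 85 per arm gives power of about 0.81 even at d = 0.44.

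Finally, outside help can indeed influence outcomes, as the article says. That is a reason to report it by arm; it does not make it a suitable covariate in an ITT model.

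**Conclusion.** The point holds and should be fixed. The plan commits to conditioning on events that follow randomisation and partly follow from the outcome, in a model it calls intention-to-treat. Leaving them out recovered the ITT effect in every scenario and kept every participant.

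The size is modest and rests on assumptions, since the documents give neither a referral rate, nor an effect of the extra care, nor the coding. With 10-30% referral in controls and a true d of 0.50, the two codings that distort the contrast give about 0.44-0.49.

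A reader might infer that the error can only hide a benefit. It cannot be read that way. With effective extra care (0.6 SD, 30% referral), the per-person × time coding gives 0.47 against a true 0.45. Under the null, with more referral in the intervention arm, it creates an apparent benefit of about 0.04-0.09 SD. Loss of up to about 15% of participants is possible, but only if medication and treatment are coded once per person.

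**What to change.** - Restrict covariates in the primary LMRA to those fixed before randomisation, for example sex, treatment center and age. Keep T0 as a time point of the outcome, as planned. The baseline score should not also be entered as a covariate, because it is already a level of the dependent variable.
- State that everyone is analysed as randomised, whatever outside help they receive.
- Report referral, medication use and treatment received by arm, over the period that both arms share (to T2).
- Move any adjustment for these variables to a labelled supplementary analysis that states its estimand, the coding of each variable and the handling of missing values.

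The cost is rewording the two covariate sentences and adding a short statement under Statistical analyses. Recruitment is complete, but no new data are needed and the sample size does not change.

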### Assessments

All assessments are self-reports and will be conducted online (except for the PHQ-2, which will be on paper for screening by the HIV nursing consultants and doctors and the PHQ-9, which will be used by the researchers for screening by telephone). Table 1 depicts all the assessment instruments that will be used in each stage of the study. The primary outcome is depression severity, as measured by the PHQ-9 [22] and the Center for Epidemiologic Studies Depression Scale (CES-D [26]). Secondary outcomes are physical tension, activation (Behavioral Activation for Depression Scale (BADS) [27]), cognitive reappraisal (Emotion Regulation Questionnaire (ERQ) [28]), cognitive coping (Cognitive Emotion Regulation Questionnaire (CERQ) [29]), depressive thoughts (Crandell Cognitions Inventory (CCI) [30]), behavioral coping (Behavioral Emotion Regulation Questionnaire (BERQ) [name] & [name], unpublished questionnaire), coping self-efficacy ([name] & [name], unpublished questionnaire), goal adjustment (Goal Disengagement and Reengagement Scale [31]), personal growth ([name] & [name], unpublished questionnaire), symptoms of anxiety (Generalized Anxiety Disorder 7 (GAD-7) [32]), negative life events (Life Events Scale, [33]), motivation to start with the intervention, compliance, dropout and reasons for dropout, medical data, and user satisfaction.

**Table 1 Tab1:** Overview of assessments during the study

Assessment	Screening HIV treatment centers *(+/- 5 minutes)*	Screening researchers *(+/- 10 minutes)*	T0: Pretest *(+/- 25 minutes)*	Three times during intervention/waiting period *(+/- 10 minutes)*	T1: post intervention/waiting period: 6-10 weeks after T0 *(+/- 20 minutes)*	T2: 3-month follow-up *(+/- 20 minutes)*	T3: 6-month follow-up^1^ *(+/- 20 minutes)*
PHQ-2 or HADS	X	-	-	-	-	-	-
PHQ-9	-	X	X	-	X	X	X
CES-D	-	-	X	-	X	X	X
Demographics and other information	-	-	X	-	X	X	X
Physical tension questionnaire	-	-	X	X	X	X	X
BADS	-	-	X	X	X	X	X
ERQ	-	-	X	X	X	X	X
CERQ	-	-	X	X	X	X	X
CCI	-	-	X	-	X	X	X
Self-efficacy questionnaire	-	-	X	X	X	X	X
Goal disengagement and reengagement scale	-	-	X	X	X	X	X
BERQ	-	-	X	-	X	X	X
Personal growth questionnaire	-	-	X	-	X	X	X
GAD-7	-	-	X	-	X	X	X
PHQ-4	-	-	-	X	-	-	-
Life Events Scale	-	-	X	-	X	X	X
Motivation	-	-	X	-	-	-	-
Compliance	-	-	-	X	X	X^1^	X
Dropout	-	-	-	X	X	X	X
Medical data	-	-	X	-	-	-	X
User satisfaction questionnaire	-	-	-	-	X	-	-

*PHQ-2* Patient Health Questionnaire 2, *HADS* Hospital Anxiety and Depression Scale, *PHQ-9* Patient Health Questionnaire 9, *CES-D* Center of Epidemiologic Studies Depression Scale, *BADS* Behavioral Activation for Depression Scale, *ERQ* Emotion Regulation Questionnaire, *CERQ* Cognitive Emotion Regulation Questionnaire, *CCI* Crandell Cognitions Inventory, *BERQ* Behavioral Emotion Regulation Questionnaire, *GAD-7* Generalized Anxiety Disorder 7, *PHQ-4* Patient Health Questionnaire 4

^1^Not sent to participants in the control group

As potential moderators of treatment outcome demographic variables (sex, age, education, and nationality), clinical and psychological characteristics (severity of depressive symptoms at baseline, anxiety symptoms at baseline, coping self-efficacy, physical health, HIV status, motivation, and alcohol and drug use) will be tested at first. Previous research indicated that some of these moderators (e.g., sex and baseline depression severity) might be important in online CBT for depression [34, 35]. In addition, other possible moderators will be investigated exploratory.

The mediator variables and the dependent variable will be measured three times during the intervention/waiting period, at the pretest, and at the first post-test. The following mediator variables will be assessed in the study: activation (two items of the BADS), physical tension (two items), cognitive reappraisal (two items of the ERQ), cognitive coping (12 items of the CERQ), goal adjustment (two items of the Goal Disengagement and Reengagement Scale), symptoms of anxiety (PHQ-4 [36]), and coping self-efficacy (two items). The dependent variable in the mediational analysis is the depressive symptoms (PHQ-4). The questions (regarding, for example, symptoms and cognitions) that will be asked during the intervention/waiting period will refer to the last week. The assessments will be administered three times during the intervention/waiting period because, at these moments, we expect change in the mediating variables. The assessments are linked to the lessons of the self-help program for participants in the intervention group. At the first measurement, we expect a change in the behavioral activation; at the second measurement, we expect a change in the physical tension; at the third measurement, we expect a change in the cognitive reappraisal and cognitive coping; and at the post-test, we expect a change in the goal adjustment. Coping self-efficacy and anxiety are expected to change over the entire course of the treatment.

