In 2014, the development of the online program was finalized, and we asked a focus group (four volunteers from the Dutch HIV Association) to evaluate the program. Thereafter, we adapted the program, and we conducted a pilot study with 20 PLH with depressive symptoms (14 males; mean age = 48.65 years, *SD* = 10.86) to test the feasibility of the program. Participants were approached via advertisements on the website and in the magazine of the Dutch HIV Association and were representative of the Dutch HIV population. The results of the pilot study showed that the program was effective in this small group; depressive symptoms decreased from pre-test to post-test. Furthermore, participants thought the program was easy to use and helpful to them. These results encouraged us to execute a large study on the effectiveness of the online self-help program.

The aim of the present paper is to describe the study protocol. The proposed study is a randomized controlled trial; the online self-help program will be compared with a waiting list control condition. The study will include a pretest and three post-tests for the intervention condition (directly after the intervention and 3 and 6 months afterward) and a pretest and two post-tests (directly after the 8-week waiting period and 3 months afterward) for the control condition. After the second post-test (5 months after the pretest), the participants in the control group can also begin the program. Concluding, we will investigate the effectiveness of the online self-help program in decreasing depressive symptoms in the short and long term. In addition, the moderators (for which patients is the program especially beneficial?) and mediators (which mechanisms affect the outcome of treatment?) will be assessed.

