### Sample size

A power analysis was performed (with the program Power Analysis and Sample Size Software: PASS; [23]) to determine the sample size needed to assess the long-term effect of the intervention on the primary outcome depressive symptoms. Based on a medium effect size of 0.50, which proved to be realistic according to the previous pilot RCT, and assuming an alpha of .05 and a power of .80, both groups should consist of 64 participants who complete the four measurements. This sample size is also large enough to detect moderate pre-defined two-way cross-product interactions, such as the interactions of group by sex. Taking into account a dropout rate of 15 % during working on the self-help program (based on our recent studies, which included coaching [21]), at least 150 patients should be allocated to the two groups at baseline (*n* = 75 in each group). We will aim for at least 200 participants because dropout will also occur during the follow-up.

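### Two unranked primary depression scales are each tested at two randomised post-tests at .05, with no primary scale, visit or success rule, so the error rate of the primary claim is not fixed

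*Protocol article*

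**What the plan says.** - **Primary outcome (Assessments).** "The primary outcome is depression severity, as measured by the PHQ-9 [22] and the Center for Epidemiologic Studies Depression Scale" (CES-D). Neither scale is placed first.
- **Model (Statistical analyses).** In the longitudinal multilevel model, "the dependent variable is the score on the PHQ-9 or the CES-D". On time: "The variable time will have four categories indicating the four time points", with T0 as reference. Each scale therefore has a separate condition effect at each post-test where both groups are measured. No contrast is called primary.
- **Significance level (Statistical analyses).** "A two-tailed alpha of .05 will be used for significance testing". The only mention of correcting for multiple tests belongs to the moderator interactions.
- **Question (Background).** "we will investigate the effectiveness of the online self-help program in decreasing depressive symptoms in the short and long term". Neither horizon is put first.
- **Sample size.** The calculation was done "to determine the sample size needed to assess the long-term effect of the intervention on the primary outcome depressive symptoms". It uses effect size 0.50, alpha .05 and power .80, and gives 64 completers per group. No scale or visit is named.
- **Control follow-up.** The Background gives "a pretest and two post-tests (directly after the 8-week waiting period and 3 months afterward) for the control condition". The footnote that Table 1 attaches to T3 reads "Not sent to participants in the control group".

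**The concern.** The protocol has one primary claim, that the programme lowers depressive symptoms, and four randomised contrasts that could carry it: two scales at two visits. As written, any of them could be presented as the primary result at .05, and the choice could be made after the results are seen. The Design section says participants, coaches and researchers cannot be blinded, and Trial status says recruitment is complete, so little else guards against a data-driven choice.

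Two things are at stake. The stated .05 may not be the error rate of the primary claim. And the sample size was set for a single test, which need not match the rule by which the trial will be judged.

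**Working it through.** **1. Reproduce the plan's figure.** Inputs from Sample size: d = 0.50, two-sided alpha .05, power .80. A two-sample t-test needs 63.8 per group, so 64, and power at 64 is 0.801. With 15% dropout, 64/0.85 = 75.3 per group, about 151 in total, against the stated 150 (75 per group). The plan's figure is reproduced, for one comparison.

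**2. Count the randomised tests.** There are two scales (Assessments). The visits shared by both groups are T1 and T2, because controls have no T3 (Background; Table 1 footnote). That makes 2 x 2 = 4 tests, or 2 if only one visit counts.

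**3. False-positive chance if any win counts, each test at two-sided .05.** For k independent tests the chance is 1 - 0.95^k:
- k = 2: 1 - 0.9025 = 0.0975
- k = 4: 1 - 0.8145 = 0.1855

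The tests are in fact correlated. The documents give no correlations, so the values below are assumptions. The correlation between two test statistics is taken as the between-scale value times the between-visit value, and the results come from multivariate normal simulation.

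| Success rule | Assumed correlations | Chance of a false positive |
|---|---|---|
| Either scale, either visit | scales .5, visits .3 | 0.169 |
| Either scale, either visit | scales .7, visits .5 | 0.149 |
| Either scale, either visit | scales .9, visits .8 | 0.108 |
| Either scale, one visit | scales .5 | 0.090 |
| Either scale, one visit | scales .7 | 0.084 |
| Either scale, one visit | scales .9 | 0.070 |
| Both scales, one visit | any | at most 0.05 |

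The last row needs no simulation: both tests being significant cannot be more likely than one of them being significant.

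**4. Power at 64 completers per group, one visit.** Assume d = 0.5 on both scales. The expected test statistic is 0.5 x sqrt(64/2) = 2.83. The last three rows come from simulation.

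| Rule | Power |
|---|---|
| One named scale at .05 | 0.80 |
| Bonferroni, a given scale at .025 | 0.71 |
| Holm, a given scale (correlation .7) | about 0.77 |
| At least one scale, .025 each (correlation .7) | about 0.83 |
| Both scales at .05 (correlation .7) | about 0.72 |

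For both scales required, power runs from about 0.70 at correlation .5 to 0.74 at correlation .8. So 64 per group gives .80 for one named scale, or for at least one of two under Holm. It does not give .80 for both scales, or for each scale after correction.

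**The case against.** The other side has several fair points.

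- **One construct.** The protocol names one outcome measured on the PHQ-9 *and* the CES-D, which could mean that both must show the effect. At one visit that rule holds the error at .05 or less. This stands as a possible reading, but the protocol does not state it, the model section joins the scales with *or*, and 64 per group does not give it .80 power.
- **A partial pointer to time.** The power statement refers to the long-term effect, so the protocol is not silent on time. This stands in part: it points to a later visit but names neither scale nor visit.
- **Detail left to an analysis plan.** Testing order and adjustment are often set there, and an article condenses. This stands for the mechanics. But choosing the primary scale and visit defines the primary outcome, and this document does define that outcome, as two scales with no visit.

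Two stronger readings are tempting.

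- **Three post-tests.** From the four time categories a reader might infer three post-tests and six tests (26.5% if independent). The documents do not support this, because controls have no T3 and no between-group test exists there.
- **Three times alpha.** A reader might also infer that the error rate simply is about three times .05. The value 0.149 needs both an any-of-four success rule and the particular correlations .7 and .5, and the protocol gives neither.

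Nor should the target of 200 be read as 85 completers per group (200 less 15%, halved) at T2. The 15% covers dropout while using the programme, and the larger target is there to absorb further follow-up losses.

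**Conclusion.** The point holds. The protocol gives two scales equal primary status, tests each at two randomised post-tests at .05, and fixes no primary scale, visit or either/both rule. The error rate of the primary claim is therefore undetermined:

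- about 11-17% if any of four results suffices (assumed correlations .5-.9 between scales and .3-.8 between visits; 18.5% if independent);
- about 7-9% for either scale at one visit (9.75% if independent);
- at most 5% if both scales are required at one visit, with power of about 0.70-0.74 at 64 per group (assumed between-scale correlation .5-.8, d = 0.5 on both).

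The sample size calculation is correct for one comparison. The protocol does not say which comparison that is.

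**What to change.** Before outcome data are analysed, name one scale at one shared visit as the single primary test. PHQ-9 at T2 is one reasonable choice: the PHQ-9 already defines eligibility and the clinically important change, and T2 is the last randomised comparison and the closest to the long-term aim of the power statement. Other choices would also do, provided they are fixed in advance. Make the other scale and visit secondary, or test them in a stated fixed order after the primary test. Sixty-four per group and .80 power then stand as written.

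If both scales stay primary, name the visit and state the rule there: Holm if either suffices, or both significant at .05. Then restate power for that rule at 64 completers per group, with the assumed between-scale correlation, using the figures in the working.

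The change takes one paragraph. The cost is that the CES-D loses equal primary status or, if both scales are kept, that per-scale power falls somewhat below .80.
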